### Study design

This is a nationwide, multicentre, prospective, single-arm intervention study in the Netherlands. Patients with irresectable stage III or metastatic melanoma who are treated with ipilimumab-nivolumab will early discontinue maintenance treatment with anti-PD-1 upon achieving a CR/PR or confirmed CR/PR according to RECIST v1.1. Figure 1 shows a schematic overview of the study design with the potential inclusion period.

**Fig. 1 Fig1:**
[figure not shown]
Design of the Safe Stop IPI-NIVO trial. Patients can be included at (confirmed) response, between three and nine months after start of treatment with ipilimumab and nivolumab. Follow-up will be conducted according to standard of care. ^1^ Response evaluation according to RECIST v1.1 [19]. Abbreviations: CR/PR = complete response/partial response, SD = stable disease

In the Netherlands, all patients with advanced or metastatic melanoma are treated in one of the 14 designated Dutch melanoma centres. The current nationwide study will be executed in all 14 centres: Amphia Hospital, Breda; Amsterdam University Medical Centres – location VU, Amsterdam; Antoni van Leeuwenhoek—Netherlands Cancer Institute, Amsterdam; Erasmus Medical Centre Cancer Institute, Rotterdam; Isala Clinics, Zwolle; Leiden University Medical Centre, Leiden; Maastricht University Medical Centre + , Maastricht; Máxima Medical Centre, Veldhoven; Medical Centre Leeuwarden, Leeuwarden; Medical Spectrum Twente, Enschede; Radboud University Medical Centre, Nijmegen; University Medical Centre Groningen, Groningen; University Medical Centre Utrecht, Utrecht; Zuyderland Medical Centre, Sittard-Geleen. In February 2023, the first site (Erasmus Medical Centre Cancer Institute) opened for inclusion.

### Study population

To be eligible to participate in this study, a patient must meet all of the following criteria:Age ≥ 18 yearsIrresectable stage III or metastatic melanomaAt least one cycle of ipilimumab-nivolumab for irresectable stage III or metastatic melanoma and considered to be a candidate for maintenance treatment with anti-PD-1;Previous systemic treatment, including immunotherapy, in the (neo)adjuvant setting is allowed;Response evaluation according to RECIST v1.1 using a diagnostic CT documenting target lesions every 12 (-2/ + 6) weeks from the start of ipilimumab-nivolumab:◦ for patients with CR on a diagnostic CT at response evaluation, a low-dose CT (which is usually part of ^18^FDG-PET/CT) is allowed at baseline◦ for patients with PR on a diagnostic CT at response evaluation, a low-dose CT (which is usually part of.^18^FDG-PET/CT) is allowed if sufficient target lesions are measurable for response evaluation according to RECIST v1.1 criteria In case of asymptomatic brain metastases prior to start of first-line ipilimumab-nivolumab, intracerebral tumour response should be confirmed using an MRI for response evaluation prior to inclusion in this study.Patients should be included after first CR/PR or first confirmed CR/PR according to RECIST v1.1Inclusion should take place no later than 5 weeks after first confirmed CR/PRIn case of SD at first response evaluation, confirmed CR/PR is required for inclusionEligible and willing to discontinue anti-PD-1 therapy within 4(+ 1) weeks after inclusion, i.e. first CR/PR or first confirmed CR/PRInclusion not later than nine months after start of treatment with ipilimumab-nivolumabPresence of MRI of the brain to screen for brain metastasis (prior to discontinuation of ipilimumab-nivolumab)Participants with previously locally treated brain metastases are eligible in case they meet the following criteria:◦ completely asymptomatic brain metastases at inclusion; an incidental epileptic seizure caused by a brain lesion is not considered an exclusion criterion◦ MRI of the brain at baseline and for response evaluation during treatment

### Follow-up

After inclusion, follow-up will be conducted according to standard of care in the Netherlands, as shown in Table 1. In the first year of follow-up, patients will visit the outpatient clinic every 12 weeks. The visits will be combined with laboratory measurements, diagnostic CT-scan for response evaluation and additional questionnaires for the quality of life. Data will be collected using the Functional Assessment of Cancer Therapy Melanoma (FACT-M), the EuroQoL Health Utilities Index (EQ-5D version 5L), the Cancer Worry Scale (CWS) and the institute for Medical Technology Assessment (iMTA) Resource Use Questionnaire Melanoma.

**Table 1 Tab1:** Follow-up scheme after first CR/PR first or first confirmed CR/PR

	**Year 1**	**Year 2**	**Year 3 and 4**	**Year 5**
**Visit outpatient clinic**	At inclusion Every 12 weeks	Every 4 months	Every 6 months	Every 12 months
**Laboratory measurements**	At inclusion Every 12 weeks	Every 4 months	Every 6 months	Every 12 months
**Response evaluation (RECIST v1.1)**	At inclusion Every 12 weeks	Every 4 months	Every 6 months	Every 12 months
**Questionnaires**	At inclusion Every 12 weeks	Every 4 months	Every 6 months	Every 12 months

### Statistics primary endpoint

The rate of ongoing response at 12 months is the primary endpoint and will be estimated using the Kaplan–Meier method and its two-sided 95% confidence interval (CI). The study will be declared positive for the primary endpoint if the lower bound of the CI is higher than 82%. A Kaplan Meier plot will be generated to illustrate ongoing response over time. This analysis will not include patients who are lost to follow-up or whose death (without progression) was not melanoma related within the 12 months after start of treatment with ipilimumab and nivolumab. These patients will not be censored, but will be excluded from the analysis for the primary endpoint. For other endpoints, data from these patients will be included in the analyses when statistically feasible. Patients who are lost to follow-up are taken into account in the sample size calculation.

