## Methods

### Primary objective

To assess the rate of ongoing response at 12 months after start of treatment in patients with advanced or metastatic melanoma who are treated with first-line ipilimumab and nivolumab and who discontinue treatment early upon achieving a (confirmed) CR or PR according to RECIST v1.1 [19]. Ongoing response is defined as ongoing complete response (CR) or partial response (PR) according to RECIST v1.1, without disease progression or melanoma-specific mortality. Death due to AEs without evidence of disease progression will not be considered progression.

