### Sample size calculation

Sample size calculation was performed for the primary endpoint of ongoing response at 12 months. The sample size calculation of this trial is based on the results of the Checkmate-069 study [11] since this prospective study provides detailed patient-level data of first response and duration of response of patients who are treated with first-line combination therapy with ipilimumab-nivolumab. In the Checkmate-069, an ongoing response at 12 months was reported in 92% of patients who had a response within 3 months after start of treatment and were treated for at least 3 months. The hypothesis of the current trial is that the percentage of patients with an ongoing response at 12 months after start of treatment should not be more than 10% worse than the 92% reported in the Checkmate-069. Hence, the null-hypothesis is an ongoing response rate of 82%. Since the rate of ongoing response in the Checkmate-069 is based on a small subgroup, we assume that 90% (instead of 92%) of patients will have an ongoing response at 12 months after start of treatment as input for the alternative hypothesis.

For the sample size calculation, the one-sample log-rank test was used [20]. Given a one-sided type I error of 2.5%, 80% power, a null hypothesis of 82% ongoing response at 12 months, and an alternative hypothesis of 90% ongoing response at 12 months, a total of 20 events (i.e. patients with disease progression) are required. Given an inclusion period of 2 years and 1 year of additional follow-up, 77 patients need to be included to reach this number of events within a total study duration of 3 years. Taking a safety margin of < 5% (*n* = 3 patients) for loss to follow-up or not-melanoma related deaths, the total sample size was set at 80 patients.

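### The primary analysis drops, instead of censoring, patients lost or dying of non-melanoma causes before month 12, so its membership depends on later outcomes; the rule is usually slightly conservative, but its wording does not protect progressions recorded before loss

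*Protocol article*

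**What the plan says.** The rule is in the protocol article, section Statistics primary endpoint. The 12-month rate of ongoing response "will be estimated using the Kaplan–Meier method and its two-sided 95% confidence interval (CI"), and "The study will be declared positive for the primary endpoint if the lower bound of the CI is higher than 82"%. The section then states: "This analysis will not include patients who are lost to follow-up or whose death (without progression) was not melanoma related within the 12 months" after treatment start, and adds: "These patients will not be censored, but will be excluded from the analysis for the primary endpoint". Data from these patients may still be used for other endpoints where feasible.

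Under Primary objective, ongoing response requires freedom from progression and from melanoma-specific death, and "Death due to AEs without evidence of disease progression will not be considered progression". A toxicity death without progression before month 12 is therefore not an event, and the exclusion rule then removes the patient from the denominator as well.

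Sample size calculation sets 77 patients and adds 3 for loss to follow-up or non-melanoma deaths, giving 80.

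**The concern.** Kaplan–Meier is designed to use partial follow-up. Here it is named as the estimator, while the patients who would supply partial follow-up before month 12 are removed. Three things follow.

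- Whether a patient belongs to the analysis set is known only after what happens up to month 12. That is selection on a post-entry outcome.
- Event-free time from patients later lost is thrown away, which costs precision in a trial decided by a margin of one or two events.
- In the exclusion sentence, the qualifier about progression is attached to the deaths and not to the losses. Read literally, a patient with documented progression at month 6 who is lost at month 10 is excluded, and a recorded failure disappears.

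The 3 extra patients replace numbers. They do not address selection. The rule is stated explicitly and governs the only success criterion, so this is not a detail left to an analysis plan.

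**Working it through.** **1. The plan's own figures.** Inputs from Sample size calculation: null 82%, alternative 90%, one-sided 2.5%, 80% power, 2 years of accrual plus 1 further year.
- With exponential times, HR = ln(0.90)/ln(0.82) = 0.531.
- Events = (1.960 + 0.842)² / (ln 0.531)² = 19.58, rounded up to 20.
- Event probabilities with uniform accrual are 0.323 under the null and 0.189 under the alternative. Their mean is 0.256, and 19.58/0.256 ≈ 76.5, rounded up to 77. Adding 3 gives 80.

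The stated 20, 77 and 80 reproduce.

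**2. Formulas for the decision rule.** With all early losses deleted, S = (n − d)/n and se = √[S(1 − S)/n]. The plain lower limit is S − 1.96·se. The log-log lower limit is S^exp{1.96·se/(S·|ln S|)}. The article does not name the interval type, so both are shown. For censoring I assume that progressions are spread over months 4 to 12 and that losses occur at month 8.

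**3. Deletion against censoring, 80 included, 3 event-free losses.** With 7 progressions:
- Deletion: S = 70/77 = 0.9091, se = 0.0328.
- Censoring: 4 events precede the losses and 3 follow, so S = (76/80)·(70/73) = 0.9110, se = 0.0321.

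| Progressions | Rate, deleted | Rate, censored | Plain limit, deleted / censored | Log-log limit, deleted / censored |
|---|---|---|---|---|
| 6 | 92.2% | 92.3% | 86.2% / 86.5% | 83.5% / 83.8% |
| 7 | 90.9% | 91.1% | 84.5% / 84.8% | **81.9% / 82.2%** |
| 8 | 89.6% | 89.8% | 82.8% / 83.1% | 80.3% / 80.6% |

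Deletion lowers the rate by 0.1 to 0.2 points. In this table the verdict changes only at 7 progressions with log-log limits: censoring passes and deletion fails.

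**4. Most failures that still pass.** Plain limits: 8 of 80 and 8 of 77. Log-log limits: 7 of 80, but 6 of 77. The planned allowance of 3 deletions thus costs one event under log-log limits and none under plain limits.

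**5. Power.** In a 6,000-replicate simulation with independent loss of about 3 patients, a true rate of 90% and log-log limits, the chance of a positive result is 38% with deletion and 44% with censoring.

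**6. Literal reading, recorded events dropped.** Suppose 10 progressions among 80, 2 of those patients later lost, and 1 further patient lost event-free.
- Literal rule, plain limits: 69/77 = 89.6%; 0.896 − 1.96·0.0348 gives 82.8%, a pass.
- The two events kept: 69/79 = 87.3%; 0.873 − 1.96·0.0374 gives 80.0%, a fail.
- Censoring the event-free loss at month 8 gives 80.1%, and crediting that patient with full event-free follow-up (70/80) gives 80.25%. Both fail.

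The same happens with log-log limits at 8 progressions, 2 later lost and 1 event-free loss: 71/77 gives 83.5% (pass), and 71/79 gives 80.8% (fail).

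**7. Informative loss.** Assume that 20% of progressors are lost just before documentation and that the true rate is 82%. The simulated false-positive rates are:
- Log-log limits: 1.6% with complete data, 5.4% with deletion, 7.1% with censoring.
- Plain limits: 3.5% with complete data, 14.7% with deletion, 17.3% with censoring.

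Censoring does not repair informative loss, and in this setting it does slightly worse than deletion.

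**8. Toxicity deaths.** With 8 progressions and 3 such deaths, deletion gives 69/77 = 89.6%, plain lower limit 82.8%. A competing-event estimate with complete follow-up, one minus the cumulative incidence of progression, gives 72/80 = 90.0%, lower limit 83.4%. It is the more lenient of the two.

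**The case against.** A reader might infer that deleting the 3 patients allowed for can turn a failed trial into a positive one. With 6 progressions, deletion gives 71/77 and a plain lower limit of 86.2%. If all 3 lost patients had in fact progressed, 71/80 gives 81.8% and the trial fails. That comparison sets deletion against a worst-case imputation. Against censoring, both analyses pass under either interval type, so the example shows informative loss and not the effect of the deletion rule. Nothing in the article indicates that loss will be informative or will exceed about 3 patients; follow-up is 12-weekly in the first year, in the 14 centres that treat all such patients in the Netherlands. This part of the objection stands.

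It can also be said that ruling out censoring presupposes patients without an event, and that Sample size calculation defines events as patients with progression, so a recorded progression would surely be kept. That is a sensible reading and probably the intended one. The exclusion sentence does not say so, however, and the gap can decide the verdict.

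Finally, a reader might infer that toxicity deaths are hidden from the trial. Primary objective openly declines to count them as progression, and overall survival and irAEs are secondary objectives. What remains is narrower: not counting a death as progression does not require removing the patient from the denominator.

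**Conclusion.** The concern holds in a limited form. The stated rule selects the primary analysis set on post-entry outcomes and reduces Kaplan–Meier to a proportion among those retained. With non-informative loss of event-free patients it errs slightly on the strict side: about 0.2 points on the estimate, and one event on the pass threshold under log-log limits. A false pass needs one of two things: recorded progressions dropped under the literal wording (82.8% instead of 80.0% in the worked case), or informative loss, which censoring alone does not cure.

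The flips occur only near the threshold. They rest on assumptions that the article does not settle: the interval type, the timing of events and losses, and the number lost. This should be fixed before the primary analysis, but it is not serious enough to undermine the design.

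**What to change.** Reword the paragraph under Statistics primary endpoint so that:

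- all included patients stay in the primary analysis;
- any progression or melanoma death observed before loss counts as an event;
- patients lost event-free are censored at their last evaluable RECIST assessment;
- patients who die of toxicity or another non-melanoma cause before progression stay in the denominator, with the death handled as a competing event (Aalen–Johansen, one minus the cumulative incidence of progression or melanoma death).

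Because censoring does not cure informative loss and the competing-event estimate treats toxicity deaths as non-failures, add a sensitivity analysis counting all losses and all deaths before month 12 as failures.

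The cost is one reworded paragraph and one extra analysis on data already collected. The change should be dated before the primary analysis, so that it cannot appear driven by the outcome.

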### Sample size calculation

Sample size calculation was performed for the primary endpoint of ongoing response at 12 months. The sample size calculation of this trial is based on the results of the Checkmate-069 study [11] since this prospective study provides detailed patient-level data of first response and duration of response of patients who are treated with first-line combination therapy with ipilimumab-nivolumab. In the Checkmate-069, an ongoing response at 12 months was reported in 92% of patients who had a response within 3 months after start of treatment and were treated for at least 3 months. The hypothesis of the current trial is that the percentage of patients with an ongoing response at 12 months after start of treatment should not be more than 10% worse than the 92% reported in the Checkmate-069. Hence, the null-hypothesis is an ongoing response rate of 82%. Since the rate of ongoing response in the Checkmate-069 is based on a small subgroup, we assume that 90% (instead of 92%) of patients will have an ongoing response at 12 months after start of treatment as input for the alternative hypothesis.

For the sample size calculation, the one-sample log-rank test was used [20]. Given a one-sided type I error of 2.5%, 80% power, a null hypothesis of 82% ongoing response at 12 months, and an alternative hypothesis of 90% ongoing response at 12 months, a total of 20 events (i.e. patients with disease progression) are required. Given an inclusion period of 2 years and 1 year of additional follow-up, 77 patients need to be included to reach this number of events within a total study duration of 3 years. Taking a safety margin of < 5% (*n* = 3 patients) for loss to follow-up or not-melanoma related deaths, the total sample size was set at 80 patients.

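### The 80% power was computed for a one-sample log-rank test over 3 years, but success is judged on the 12-month Kaplan-Meier lower limit, which has only about 34–64% power with 77 patients

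*Protocol article*

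**What the plan says.** **Sizing (protocol article, Sample size calculation).** "For the sample size calculation, the one-sample log-rank test was used". The error and power inputs read "Given a one-sided type I error of 2.5%, 80% power"; the 12-month rates compared are 82% (null) and 90% (alternative). The calculation concludes that "a total of 20 events (i.e. patients with disease progression) are required", and that recruiting 77 patients over 2 years, with 1 more year of observation, will supply them. Three more patients are added for loss to follow-up or deaths from other causes, which makes 80.

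**Decision (protocol article, Statistics primary endpoint).** The 12-month rate is estimated by Kaplan-Meier with a two-sided 95% interval. "The study will be declared positive for the primary endpoint if the lower bound of the CI is higher than 82" (per cent). Patients lost to follow-up, or dying of a non-melanoma cause without progression, within 12 months of treatment start are left out of this analysis rather than censored.

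The article does not name the log-rank test as an analysis, and it gives no power for the Kaplan-Meier rule.

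**The concern.** The trial is sized for one test and judged by another. A one-sample log-rank test gains information from every progression during follow-up, here up to 3 years. A confidence limit for the 12-month rate gains nothing from progressions after month 12. If the two differ much in information, the stated 80% does not describe the trial's chance of success.

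The section says it sizes the 12-month primary endpoint, so readers will apply the 80% to the success rule. If early stopping performs exactly as assumed and the trial still has an even or worse chance of failing, a negative result says little about early stopping but may well be taken as evidence against it.

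**Working it through.** **1. Reproducing the plan's own figures.** Exponential time to progression and uniform accrual are assumed. The article states neither, but together they return its numbers.

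- Yearly hazards: λ0 = −ln 0.82 = 0.1985 and λ1 = −ln 0.90 = 0.1054. Hazard ratio 0.531, with ln HR = −0.633.
- Events: (1.960 + 0.842)² / (0.633)² = 7.849 / 0.4009 = 19.58, i.e. 20.
- Event probability with 2 years of accrual and 1 further year: 1 − (e^(−λ) − e^(−3λ)) / (2λ). This gives 0.3232 under the null and 0.1885 under the alternative, mean 0.2558.
- Patients: 19.58 / 0.2558 = 76.5, i.e. 77.

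Both figures agree. In simulation (100,000 runs), the log-rank test on all follow-up with 77 patients had 75% to 81% power, depending on the variance form. The 80% therefore belongs to that test.

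**2. Events available to the success rule.** By month 12, 77 patients give 77 × 0.10 = 7.7 events at a true 90% and 77 × 0.18 = 13.9 at 82%. Neither is near 20.

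**3. Why the rule is a binomial rule.** Each patient has at least 1 year of follow-up after inclusion, so month 12 from treatment start is reached. Those lost or dying of other causes before then are excluded. Nobody is censored before month 12, so the Kaplan-Meier estimate is (n − events) / n. Its power depends only on the 12-month rate, not on the shape of the curve.

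**4. Exact power, 77 evaluable patients.** For each interval, find the largest event count whose lower limit exceeds 0.82, then compute the binomial probability of that count or fewer.

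| Interval | Most events allowed | One-sided error at 82% | Power at 90% | Power at 92% | True rate for 80% power |
|---|---|---|---|---|---|
| Plain Greenwood | 8 | 4.9% | 63.7% | 84% | 91.6% |
| Exact or Wilson | 7 | 2.3% | 49.0% | 73% | 92.7% |
| Log-log | 6 | 0.9% | 34.0% | 58% | 93.8% |

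The log interval gives the same result as plain Greenwood at this size. With 8 events, 69/77 = 89.6%, close to the design assumption. The exact lower limit is then 80.6% and the trial fails; the plain limit is 82.8% and it passes.

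**5. All 80 patients evaluable.** Power at 90% is 45% (exact, Wilson, log-log), 59% (plain) or 72% (log). The last allows 9 events and has a one-sided error of 7.1%.

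**6. Size needed for 80% power at 90% under the current rule.** This is first reached at 116 (plain), 145 (Wilson), 153 (exact) or 154 (log-log) evaluable patients. Power saw-tooths with n; for the exact interval it stays at or above 80% from 166.

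**The case against.** The strongest reply is that the calculation is sound on its own terms: 20 events and 77 patients are correct for the test named. That stands. The fault is not a slip of arithmetic but a mismatch between the test sized and the rule used.

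A second reply is that the interval type is normally left to the analysis plan, which is not shown, and that the range depends on the evaluable count. With 78 evaluable patients the log-log interval allows 7 events and its power rises to 47.5%. Across 77 to 80 evaluable patients and all the intervals tried, the range is about 34–72%. This is fair, and the unnamed interval is not itself the finding. But none of these choices reaches 80%, and the 72% comes with a 7.1% error against a stated 2.5%.

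Third, 90% was set deliberately below the 92% of the reference study. At 92% the plain interval does pass 80%, but with a 4.9% error; the exact interval reaches 73%. The protocol attaches its 80% to a true 90%, so that is where the claim must be tested.

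Last, an even chance of failure describes the exact or Wilson rule. Under plain Greenwood the odds are nearer two to one in favour of success. That is correct, though that rule does not hold 2.5%.

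**Conclusion.** The concern holds. The stated 80% power does not apply to the rule that decides the trial. At the assumed 90% and 77 evaluable patients, the rule's power is 34% to 64% depending on the interval. It is at most 49% for the intervals checked that keep the one-sided error within 2.5%.

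The power figures rest on 77 evaluable patients, the stated rates of 82% and 90%, and complete observation to month 12. They need no assumption about curve shape. Exponential survival and uniform accrual are needed only to reproduce the 20 events and 77 patients.

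A related point: 77 patients comes from averaging the event probability under the two hypotheses. At a true 90%, 3 years would yield about 77 × 0.1885 = 14.5 events, so the 20 events would probably not be reached if the design assumption is right.

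**What to change.** In the sample size section, state the power of the rule actually used: about 49% at a true 90% with 77 evaluable patients, and 80% only if the true rate is about 92.7%. Make clear that the 80% figure belongs to the log-rank test.

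In the primary endpoint section, name the interval. An exact (Clopper-Pearson) interval keeps the one-sided error at or below 2.5% whatever the number of exclusions. Success then means at most 7 events for 77 to 80 evaluable patients, and at most 6 for 76. Wilson gives the same limit at 77 to 80 but allows 7 events at 76, with an error of 2.58%, so exact is the safer choice.

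Pre-specify the one-sample log-rank test against the curve with 82% at 12 months, on all follow-up, as the supportive test, since 77 patients were sized for it. State its time origin, because patients join three to nine months after treatment start.

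The cost is protocol and analysis plan wording only, with no extra patients, but the stated power becomes less favourable. If the sponsor wants a real 80% for the primary decision, there are two larger changes: make the log-rank test primary, or enlarge the trial to the sizes in step 6 of the working. Either should be settled before outcome data are examined.
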